### Data management and analysis

Statistical analyses will be both cross-sectional and longitudinal, according to the specific study component under analysis. Descriptive analyses will explore distributions and baseline associations between key exposure (provision or use of integrated services), outcomes and potentially confounding variables. Multivariable logistic regression modeling will be used to analyse study outcomes in HFA data (CPI observation data and client exit interviews), client cohort data, client flow data, community survey data and periodic activity review data.

To measure the magnitude of changes in the quality of services provided, composite summary scores will be developed from a series of key items assessed during CPIs. The composite score will be developed from a set of activities providers are required to perform or ask during history-taking for each CPI observed. The items will be based on an accepted standard of quality adapted from the national guidelines. Analyses of facility data will be undertaken and the average mean scores and the proportion of women receiving an acceptable quality of service will be calculated from the composite scores for each set of indicators.

Survival analysis will be conducted with the client cohort data to evaluate the effect of integration on key outcomes over time (up to 24 months follow-up), using two approaches: 1) comparing the cumulative probability of outcomes among clients who received services in intervention versus comparison clinics at the time of recruitment (i.e. an intent-to-treat analysis); and 2) assessing a dose–response relationship between clients’ cumulative exposure to integrated services over the duration of the study.

To evaluate exposure to integrated services, an ‘index of integration’ will be developed. A generalized latent variable will be modeled using data from the client flow analysis and costing tools and validated by testing it against expert opinion (both researchers and service practitioners), to give each clinic a ranking score for its level of integration at various points in the study cycle. The index will be used to: a) assess changes in the extent of integration within each facility over time (whether originally allocated as intervention or not); b) control for baseline differences in integration when comparing outcomes in intervention and comparison facilities; and c) measure changes in the extent of integration over time and apply as a time-varying exposure in the dose–response analysis described above.

Qualitative data will be captured in digitally recorded files, transcribed and translated (where needed), before being exported into QSR Nvivo 8 software for management and analysis. A thematic framework will be used in qualitative analysis, allowing a fusion of both a deductive approach, with themes pre-identified from the study objectives, and an inductive approach, with themes emerging from the data incorporated into ongoing analyses.

The economics findings will be used to explore whether there are economies of scope and scale associated with the provision of an integrated package of SRH-HIV services, and to explore the relative efficiency of different models of provision. Cost data will be captured in specially designed Excel spreadsheets. These will then be entered into a STATA dataset. The impact of integration on efficiency will be assessed using a combination of parametric and non-parametric methods. Descriptive cost and resource use analysis, uni-variate analysis and Data Envelopment Analysis (DEA) will be used to identify those clinics that are more or less efficient; changes in unit costs, resource use, resource sharing and efficiency between baseline and endline; and to explore possible explanations for efficiency changes. Intervention and comparison sites will be compared, but also within these different sites with one another.

In addition, a multi-level multivariable logistic regression analysis will be used to explore any association between unit costs, the intervention and integration. This will first explore the relationship between patient level characteristics and costs (derived from a combination of cohort data with cost data) and then, taking this into account, between facility level characteristics and costs. The integration index will be included as a facility level characteristic. Data from the cohort study will provide client level characteristics and service use. This will be combined with the unit cost data to estimate client level (health service) costs. Data from the periodic activity review data and health facility assessments will be used to define facility characteristics.

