#### Sampling and indicators

Details on research methods are provided below; sampling strategy and sample size calculations for each method are summarised in Table 2.

The operational results (outcomes) and the main indicators that will be measured and analysed for each study objective are shown in Table 3.

**Table 3 T3:** Operational results and indicators to be used to compare results from the intervention and comparison health facilities

**Objective 1. Determine the benefits of different integrated models to increase range, uptake and quality of selected SRH and HIV services and to diversify the profile of clients.**		
**Results/Outcomes**	**Indicators**	**Data source**
Feasibility of linking services demonstrated	Number of internal and external referrals, Number of staff updated in HIV counseling and testing Number of staff updated in HIV BCC prevention, Facilities have adequate equipment and supplies	Service statistics Provider interviews Facility inventory
Provision of linked services to clients	Clients received CT in FP consultation, Clients referred for ART, Clients referred for other services, Number of referrals attended, Proportion of population demanding integrated services, Proportion of population accessing integrated services, Proportion of services users giving integration as a reason for choice of clinic	Client exit Provider interview Cohort Community Survey
Increased % of eligible HIV+ women starting to use ART	Proportion of women reaching referral site clients know their CD4 counts	Service statistics Cohort
Increased uptake of range of SRH services including integrated CT, FP, PNC and STI screening services	% FP clients accessing more than one service Proportion of population accessing more than one service at last FP or PNC visit	Service statistics Exit /Cohort Community Survey
Increased quality of a range of SRH services	% clients receiving minimum level of quality services	Client – provider interaction, exit interview
Increase in number and diversity of clients	% men and women using component services Proportion of clients using component services by age, SES and gender	Community Service Statistics Client exit /CPI
Increased numbers of clients screened/managed for STIs	% FP clients accessing separate/integrated services	Service statistics Client Flow Cohort
Increased in new and repeat FP clients testing for HIV		Service statistics Cohort

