This component entails a structured non-participatory observation of health consultations, encompassing both the counseling process (how clients are treated and whether they actively participate) and the technical content of a consultation (provision of essential information and its technical accuracy). To reach a meaningful measure of quality of care with a relatively small sample size for the FP-HIV model, 18 consecutively sampled new FP clients and 18 revisit FP clients (assuming 6 clients for an average of three health providers in each facility) will be observed. For the PNC-HIV model in Kenya and Swaziland, 24 consecutively sampled postpartum women (between 6 to 8 postpartum women observed: within 48 hours of birth, between one to two weeks and around six weeks postpartum) per study facility. We acknowledge that observing client provider interaction may bias in a positive direction the results obtained on quality of care. We will spend more than one day at each site, so that the presence of the research team becomes more familiar and the behavior of the providers becomes more normative, furthermore over the three to four year data collection period the presence of researchers will become very familiar to the staff.

iv) Client exit interviews

Exit interviews will be held with each client who was observed to ascertain their perceptions of and satisfaction with the service received, as well as their SRH and HIV-related behaviors and fertility intentions.

v) Client flow assessment

A five-day assessment of service utilisation patterns will be conducted at each facility, biannually in Kenya, and annually in Swaziland, to measure: the total number of clients at each facility (per day); the service type being sought; the extent of service integration and referrals; and waiting times. Client data will also be captured including age, sex, and residence (proximity to the health facilities). All clients entering the facility for MCH services over the five-day period will be asked to participate, and given a client flow instrument by research assistants and/or service providers. Clients will carry the form throughout their consultations: every service provider seen will complete the form, indicating session start/end times, service(s) received and services referred for.

b) Prospective routine monitoring

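### The only model named for the quality-of-care observations is logistic, so the modelled comparison is pass/fail and the more informative mean composite score is only calculated

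*Protocol article*

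**What the plan says.** Under Data management and analysis, the article gives the purpose of the score: "To measure the magnitude of changes in the quality of services provided, composite summary scores will be developed". Two summaries will be taken from it: "the average mean scores and the proportion of women receiving an acceptable quality of service will be calculated from the composite scores".

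The same section names one inferential model for the client-provider interaction (CPI) observations: "Multivariable logistic regression modeling will be used to analyse study outcomes in HFA data (CPI observation data and client exit interviews". The sentence goes on to the client cohort, client flow, community survey and periodic activity review data. No linear or other continuous-outcome model is named for the quality score.

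Table 3, Objective 1, gives one indicator for increased quality, a percentage: "clients receiving minimum level of quality services". The mean score is not listed there.

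On sample size, the CPI subsection under Description of methods and data collection explains its choice for one model: "To reach a meaningful measure of quality of care with a relatively small sample size for the FP-HIV model". It then gives "18 consecutively sampled new FP clients and 18 revisit FP clients", and 24 postpartum women per facility for the PNC model. Table 2 gives 18 per facility for every model. No cut-off, SD, effect size or power is stated for this component.

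**The concern.** Ordinary logistic regression needs a binary outcome. Read with Table 3, it means that the planned statistical comparison of quality is of the share of clients above a cut. That does not match the stated purpose of the score. A rise from very poor to just below the cut counts as nothing, while a small step across it counts in full. The result also depends on where the cut is placed.

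Quality of services is a named part of Objective 1, and the observation samples are modest. If the pass/fail comparison is the one that carries the inference, a real improvement is more likely to be reported as no clear difference than it would be with the score itself, which is collected and averaged anyway.

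**Working it through.** There is no power figure for the CPI component to reproduce; 80% power is stated only for the cohort and the household survey. The check therefore compares the two analyses on the same data under stated assumptions.

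**Inputs from the article**
- Facilities per arm: 6 in each Kenya model and 4 in Swaziland as planned. A Table 2 footnote says that 2 facilities were added later.
- Table 2, 18 observations per facility: 6 × 18 = 108 per arm in Kenya, 4 × 18 = 72 in Swaziland.
- Text, FP: 18 + 18, read as 36 per facility, so 6 × 36 = 216 per arm.
- Text, PNC: 24 per facility, so 6 × 24 = 144 per arm in Kenya and 4 × 24 = 96 in Swaziland.

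**Assumptions (not in the article)**
- Normal score, two-sided 5%, one post-intervention round.
- Shift d in SD units, share p1 acceptable in the comparison arm, intra-facility correlation (ICC).

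**A. Ignoring clustering**
- Score: two-sample t-test with noncentrality d × √(n/2). For n = 108 and d = 0.4 this is 0.4 × √54 = 2.94, giving power 83%.
- Pass/fail: p2 = Φ(Φ⁻¹(p1) + d), then a two-proportion z-test. With p1 = 0.50, p2 = Φ(0.4) = 0.655.
  - Pooled SE = √(2 × 0.578 × 0.422 / 108) = 0.0672.
  - Unpooled SE = √((0.250 + 0.226) / 108) = 0.0664.
  - Power = Φ((0.1554 − 1.96 × 0.0672) / 0.0664) = Φ(0.36) = 64%.

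| n per arm, d | Score | Cut at 50% acceptable | 20% | 10% |
|---|---|---|---|---|
| 108, 0.4 | 83% | 64% | 58% | 46% |
| 72, 0.5 | 85% | 65% | 60% | 49% |
| 144, 0.35 | 84% | 65% | 58% | 46% |
| 216, 0.3 | 88% | 70% | 62% | 49% |

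The loss is 18 to 20 points at the mid-range cut, 25 to 26 at 20% and 36 to 39 at 10%. For a very large effect it disappears: with n = 144 and d = 0.8, both analyses have power of about 100% at mid-range cuts.

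**B. Analysing facility means**
- Score: variance of the difference = (2/k) × (ICC + (1 − ICC)/m), for k facilities per arm and m clients each, tested on 2k − 2 degrees of freedom. For k = 6, m = 18, ICC = 0.02 this is (1/3) × (0.02 + 0.98/18) = 0.0248, SE 0.158. For d = 0.5 the noncentrality is 0.5/0.158 = 3.17 on 10 df, giving power 82%.
- Pass/fail: facility proportions from the same simulated scores (20,000 runs), compared by t-test.

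| Facilities × clients, ICC, d | Score | 50% cut | 20% cut |
|---|---|---|---|
| 6 v 6 × 18, 0.02, 0.5 | 82% | 67% | 62% |
| 6 v 6 × 18, 0.05, 0.5 | 68% | 57% | 54% |
| 4 v 4 × 18, 0.02, 0.6 | 74% | 59% | 57% |
| 4 v 4 × 18, 0.05, 0.4 | 32% | 27% | 24% |
| 6 v 6 × 24, 0.05, 0.5 | 74% | 64% | 61% |
| 6 v 6 × 36, 0.05, 0.5 | 81% | 72% | 70% |

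The loss is 10 to 20 points in most rows, 5 to 8 where power is only about 32%, and 9 to 11 at 36 clients per facility. It persists under the Table 2 counts and under the larger counts in the text.

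**The case against.** The strongest reply is that the continuous score is not thrown away. The mean is calculated, is named before the proportion and is not marked as secondary. This part stands: a reader might infer that the score is reduced to a pass/fail proportion, and the text does not support that. What the text lacks is a comparison model for the mean.

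A second reply is that a condensed article leaves model detail to an analysis plan. That would answer a complaint about silence. Here the article does name a model for the CPI data, and Table 3 names only a percentage. The point concerns that stated choice.

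Third, the logistic sentence is generic. It covers several data sources, and CPI data include yes/no items for which logistic regression is natural. The list of methods is also not exclusive, since survival analysis is added for the cohort. This is fair, and it is why the point is an improvement and not an error.

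Fourth, whether clients reach a minimum standard is a legitimate, policy-readable question, particularly for the adequacy part of the evaluation, and the CPI sample was not sized on power. That supports keeping the percentage; it does not support making it the only modelled form.

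Finally, a reader might quote a single loss of power as a property of this study. The documents do not fix one: effect, SD, cut and ICC are all assumed, and across a wider grid of assumptions the loss runs from 0 to about 46 points. The remark about a relatively small sample is also made only for the FP-HIV model and should not be extended to the others.

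**Conclusion.** The point holds in a limited form. The article calculates both summaries, but the only model it names for CPI data is logistic and the only quality indicator in Table 3 is a percentage. The inferential comparison as written is pass/fail, which is a poor match for a score meant to measure the size of change.

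For a normal score at two-sided 5% in one round, the cost is typically about 10 to 20 points of power when facility means are analysed, and about 5 to 10 where power is already low. Ignoring clustering, it is about 18 to 20 points at a mid-range cut, more at extreme cuts and close to zero for very large effects. With 4 to 6 facilities per arm, clustering limits power under either analysis. This is a cheap improvement; it does not show that the planned analysis is invalid.

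**What to change.** - In Data management and analysis, make the composite CPI score the main quality comparison. Use a linear model for intervention by round with facility as the cluster, or a comparison of facility mean scores, and report the mean difference with a 95% CI.
- In Table 3, add the mean composite quality score as an indicator for increased quality.
- Keep the percentage at an acceptable or minimum level as a secondary indicator, with its cut fixed in advance.
- Keep logistic regression for health facility assessment outcomes that are truly binary.
- Reconcile the CPI counts in Table 2 (18 per facility) with the text (FP 18 + 18, PNC 24), so that the precision of the comparison can be stated.

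The cost is wording in one section and one Table 3 row, with no new data. The downside is that a mean difference is less readable for policy users, which is why the percentage stays.

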#### Selection of intervention study sites

The study will be implemented in public health facilities in Central and Eastern provinces in Kenya and in three regions in Swaziland. Six intervention facilities from two districts in Central Province were selected from the original 23 facilities participating in the previous integration study using FP as the entry point [30] and building on that experience. The two criteria for selecting intervention facility selection were: i) good performance in the previous study and ii) high throughput of FP clients (≥100/month). These six intervention facilities include two hospitals and four health centres. In order to match these sites with six comparable sites in the same province and avoid contamination, additional criteria (see below) were used to randomly select facilities with similar characteristics from outside the two original study districts.

The existing four facilities (public health units/MCH-FP) from the previous study in Swaziland [31] were selected as the intervention facilities. In order to match these sites with four comparable sites and avoid contamination, criteria were used to select the comparison facilities that have similar characteristics but away from original study sites. Sites that fitted the criteria (see below) were visited in July 2008 by Population Council, London School of Hygiene & Tropical Medicine (LSHTM) and the MOH and assessed for comparability to the intervention sites. In discussion with the Provincial Health Management Team for Eastern Province, Kenya we were advised not to continue with the district from the previous study [20]. This was due to the high number of other health sector interventions. Therefore, two districts with limited external support were selected and randomly allocated as intervention and comparison sites.

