#### Selection of comparison study sites

To maximize equivalence between the intervention and comparison facilities, thereby minimizing selection bias, a pair-wise matching sampling design will be used. Comparison facility selection will be based on four criteria, namely: high client load (> 50 infants/month receiving their first immunizations at 6 weeks at the PNC-HIV clinics and >100 FP clients/month at the FP-HIV clinics); a minimum of two providers qualified in and currently delivering FP services; a range of services available (FP, voluntary counseling and testing (VCT), STI treatment, prevention of mother-to-child transmission (PMTCT); and no current provision of fully integrated PNC-HIV and FP-HIV services. Facilities allocated to each study model serve populations with similar socio-economic characteristics, have a similar health infrastructure (i.e. public sector), and serve a population with a relatively high modern method contraceptive prevalence rate and similar HIV prevalence among women aged 15 to 49 years. To minimize contamination, the facilities’ (with comparable characteristics) will be selected in different districts in the same province. The number of facilities that will be purposively selected for each model and country are summarized in Table 2.

**Table 2 T2:** Sampling strategy and sample size calculations for each Integra research component

**Research Component**	**Sampling strategy**	**Key indicators used in sample size calculation**	**Adjustments to sample calculation**	**Model 1. Kenya FP**	**Model 2. Kenya PNC**	**Model 2. Swaziland PNC**
Sampling of facilities	Theoretical sampling to point of saturation within province	4 criteria: high client load; minimum of 2 FP providers; range of SRH services available; no current provision of SRH-HIV integration	n/a	12 facilities: 6 Intervention and 6 Comparison	12 facilities: 6 Intervention and 6 Comparison	8 facilities: 4 Intervention and 4 Comparison*
HFAs: Facility inventory				1 per facility	1 per facility	1 per facility
HFAs: Client exit interviews & linked observations of consultations	Consecutive sample and saturation	Quality of Care analysis 6 CPIs	No	18 per facility: 6 new clients, 6 repeat clients and 6 clients switching FP method	6 within 48 hours postpartum 6 at one week and 6 at 6 weeks per facility	6 within 48 hours postpartum 6 at one week and 6 at 6 weeks

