***Qualitative – in-depth interviews***						
Providers	Convenience sampling			1-3 providers per facility	1-3 providers per facility	1-3 providers per facility
Cohort clients	Purposive sampling to reflect issues emerging from quantitative data		25 HIV-positive clients; and 25 other clients	25 HIV-positive clients; and 25 other clients	25 HIV-positive clients; and 25 other clients	
Community members	Purposive sampling to reflect issues emerging from quantitative data		20 men	n/a	20 men	

* 2 facilities subsequently added due to lower than expected client load at comparison sites.

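### The client-level logistic and survival models named for the cohort and facility-assessment effects carry no allowance for facility clustering, although integration is assigned by facility with 4 to 6 facilities per arm

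*Protocol article*

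**What the plan says.** Integration is a property of the facility. Table 2 gives "12 facilities: 6 Intervention and 6 Comparison" for each Kenya model and "8 facilities: 4 Intervention and 4 Comparison" for Swaziland, with the footnote "2 facilities subsequently added due to lower than expected client load at comparison sites". Comparison sites are chosen to resemble intervention sites: "a pair-wise matching sampling design will be used". For Kenya PNC, Selection of intervention study sites says that "two districts with limited external support were selected and randomly allocated as intervention and comparison sites", which is one district per arm.

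Data management and analysis then names the effect models. The first is: "Multivariable logistic regression modeling will be used to analyse study outcomes in HFA data (CPI observation data and client exit interviews), client cohort data"; the same sentence goes on to client flow, community survey and periodic activity review data. For the cohort there is also a survival analysis, whose first approach is "comparing the cumulative probability of outcomes among clients who received services in intervention versus comparison clinics at the time of recruitment". Neither statement mentions a facility random effect, frailty, GEE, robust variance or cluster-level summary.

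Clustering is provided for in two other places. The cost analysis says "a multi-level multivariable logistic regression analysis will be used to explore any association between unit costs, the intervention and integration", and the household survey sample size carries a design effect of 2.0. The cohort adjustments in Table 2 are 30% loss to follow-up and over-sampling of HIV-positive clients, with no design effect.

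**The concern.** Clients of one clinic share staff, supplies, catchment and local practice, so their outcomes are correlated. When the exposure varies only between clinics, the information on it is limited by the number of clinics. A client-level model that treats several hundred clients per arm as independent counts ordinary between-clinic variation as evidence about integration.

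The intervention-versus-comparison contrast is the first strand of plausibility evidence listed under Approach and conceptual framework. If its intervals are too narrow, a chance difference between a few clinics can be reported as an effect of integrated services. With so few clusters, an uncorrected sandwich variance would not fully cure this either.

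**Working it through.** **Inputs from the article.** Facilities per arm k: 6 (each Kenya model) and 4 (Swaziland). Cohort recruits per arm: 976 (Kenya) and 989 (Swaziland). Loss: 30%. Power: 80%. Condom use: 5% to 10% (Kenya), 13% to 20% (Swaziland). Facility-assessment clients per facility: 18 (Table 2), 24 (PNC text) or 36 (FP text, 18 new plus 18 revisit).

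**Assumed, because not given.** ICC 0.005 to 0.05, equal facility sizes, alpha 0.05.

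**Step 1: the article's own sample size.** The two-proportion formula with pooled variance, two-sided, gives 435 (Kenya) and 441 (Swaziland) per arm. Allowing for loss, 435/0.7 = 622 and 441/0.7 = 630. The stated 976 and 989 do not follow from these inputs: 976/622 = 1.57 and 989/630 = 1.57. A one-sided test (343 and 347) with a doubling comes close: 2 × 343/0.7 = 980 and 2 × 347/0.7 = 991. An undeclared clustering allowance is therefore possible.

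**Step 2: retained clients per facility, m.** Kenya: 976 × 0.7/6 = 114. Table 2 is broken here, so 976 may cover both Kenya models: 976 × 0.7/12 = 57. Swaziland: 989 × 0.7/4 = 173.

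**Step 3: understatement.** Design effect DEFF = 1 + (m − 1) × ICC. The correct interval is √DEFF times the client-level width. The true error of a nominal 5% client-level test is 2Φ(−1.96/√DEFF). Example, Kenya at ICC 0.01: DEFF = 1 + 113 × 0.01 = 2.13, √2.13 = 1.46, 1.96/1.46 = 1.34, error 18%.

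| Setting | DEFF, ICC 0.005 to 0.05 | Width ratio | True error |
|---|---|---|---|
| Kenya cohort, 6 v 6, m 114 | 1.56 to 6.64 | 1.25 to 2.58 | 12% to 45% |
| Kenya cohort, 12 v 12, m 57 | 1.28 to 3.80 | 1.13 to 1.95 | 8% to 31% |
| Swaziland cohort, 4 v 4, m 173 | 1.86 to 9.60 | 1.36 to 3.10 | 15% to 53% |

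The arm of the two added Swaziland facilities is not stated. At 5 v 5 the width ratio is 1.30 to 2.81 and the error 13% to 49%.

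For facility-assessment data with 18 to 36 clients per facility, ICC 0.01 gives a ratio of 1.08 to 1.16 (error 7% to 9%), and ICC 0.05 gives 1.36 to 1.66 (15% to 24%).

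**Step 4: simulation.** A beta-binomial simulation with no effect (20,000 replicates per setting) gave client-level error of 12%, 17%, 28% and 45% (Kenya, 6 v 6) and 16%, 24%, 35% and 53% (Swaziland, 4 v 4) at ICC 0.005, 0.01, 0.02 and 0.05. A t test on cluster means stayed at 4% to 5%.

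**Step 5: few clusters.** A t reference on 2(k − 1) degrees of freedom in place of 1.96 widens intervals by a further 2.228/1.960 = 1.14 (k = 6) or 2.447/1.960 = 1.25 (k = 4).

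**Step 6: does a larger sample help?** At ICC 0.01 in Kenya, the 435 retained clients per arm implied by the stated inputs would mean m = 72.5, DEFF = 1.715 and error 13%. The larger stated sample gives m = 114 and error 18%. Inflating the sample can protect power but raises the error of a client-level test.

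**The case against.** The strongest defence is that this is a condensed article. A reader might infer that the investigators intend to ignore clustering and reserve multi-level models for costs, but no sentence says so. The logistic sentence names a model family for five data sources, including the community survey, which the article elsewhere treats as clustered. Variance details may sit in a fuller plan, and the unexplained inflation in 976 and 989 is compatible with an allowance for clustering. All of this stands against any claim that clustering was overlooked. It does not remove the point: the article names the effect models, names no facility term for them, and names one for costs. A larger sample does not correct the error rate.

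A reader might also call the intervals far too narrow without condition. That needs an ICC the documents do not give. At 0.005 the cohort understatement is modest, and for facility-assessment data at 0.01 it is small. The figures are for an unadjusted two-proportion comparison. Covariates, including the facility integration index, could absorb some between-clinic variation, but the index is a covariate or exposure and does not supply a variance term. The survival and dose-response analyses were not simulated.

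Nor do the documents show that the pair matching will be dropped in analysis. If it were, leaving out a positively correlated match usually makes standard errors larger, so matching does not support the claim of narrow intervals.

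Finally, the plausibility case does not rest on the arm contrast alone. The article lists five strands, including change over time, dose-response and triangulation.

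**Conclusion.** The point holds in a limited form. The cohort and facility-assessment effect models, as named, make no allowance for the facility as unit of assignment, and following them literally gives anti-conservative intervals and P values. For the cohort, the true error of a nominal 5% test is about 12% to 45% in Kenya (8% to 31% if 976 per arm spans both models) and about 15% to 53% in Swaziland at 4 v 4. For facility-assessment data it is 7% to 9% at ICC 0.01 and 15% to 24% at ICC 0.05. These figures rest on the assumed ICC, equal facility sizes and 30% loss. The direction does not depend on the exact ICC, provided it is positive.

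Kenya PNC raises a separate matter. Cohort clients are recruited only after the post-intervention facility assessment, so the cohort has no pre-intervention measurement. With one district per arm, its arm contrast cannot be separated from district, and a facility clustering term does not cure that.

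**What to change.** In Data management and analysis, name facility as the cluster for cohort, exit-interview and client-provider observation outcomes. Either use facility-level summaries with a t test on 2(k − 1) degrees of freedom, or use mixed or GEE models with a small-sample correction. Add a facility frailty to the survival models. State the ICC, alpha and sidedness behind 976 and 989, and whether 976 applies to each Kenya model.

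For Kenya PNC, state that between-arm P values are conditional on district. Rest inference there mainly on change from the pre-intervention facility assessment and on dose-response, both already among the article's strands of evidence.

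The cost is a few sentences and modest programming. Intervals will be wider, and power falls with them: at 6 v 6 in Kenya with 30% loss, power by the normal approximation runs from about 80% at ICC 0.005 to 27% at 0.05.
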